### Procedure and allocation

Recruitment will take place in a large urban area in the Netherlands. School boards in the study area will be informed about the study and asked to make their teachers aware of it. Teachers will also be recruited by social media and by presentations at schools. Interested teachers will receive an information leaflet and be invited for a screening interview by telephone. Teachers who are willing to participate will provide written informed consent which will be obtained by one of the researchers ([name]).

Participants will receive online questionnaires, which will be processed anonymously. Questionnaires will be administered before and after the MBSR or wait list period (September and November), and at 3 months’ follow-up (March). As participants will be aware whether they have or have not participated in the course by the time they complete the follow-up assessments, they cannot be kept completely blinded. We will compare data related to teacher absenteeism from the school year prior to that in which they participate in the research. After completion of the follow-up, teachers of the control group will be offered the MBSR programme as well. To include the required 155 participants, the intervention procedure between September and June will be repeated for three consecutive school years.

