### Sample size calculation

In determining the necessary number of participants, we have presumed a significance level (α) of 0.05 and a moderate effect size (δ) of 0.50 (e.g. Verweij et al, 2016). To achieve a power of 80%, we will need to include 64 participants in the intervention as well as the control group. With an estimated 17.5% drop-out, which is comparable to a similar study by Verweij et al, (2016), we will strive to recruit 155 participants divided over three school years.

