#### Effectiveness

The primary analyses will be based on the intention-to-treat principle and linear mixed models (LMMs) will be used for the primary analyses. LMMs adequately deal with missing data at random and can be used to account for the hierarchical structure of the data (i.e. multiple assessments nested within teachers, teachers nested within groups and schools). Time, condition and time by condition interactions will be specified as fixed factors to examine the effect of the intervention over time on primary and secondary continues outcomes. Baseline scores of the corresponding outcome will additionally be entered in the model to account for baseline imbalances. In accordance with the CONSORT statement, we will not statistically test whether the two groups differ in baseline variables. Therefore, the models that we will primarily report will not be adjusted for additional covariates. However, to examine whether adjusting the model for additional covariates substantially changes conclusions drawn from the analyses, we will conduct sensitivity analyses with the models adjusted for the following potentially confounding baseline variables: sex, age, school weight, teachers’ years of experience, number of work days per week and past or present psychological problems. All models will also be run with completers only as additional sensitivity analysis. Post hoc tests will be conducted for between-group differences at each timepoint using analyses of covariance (ANCOVA), including baseline scores of the corresponding outcome as covariate. Estimated marginal means and corresponding standard errors from the primary LMMs will be used to additionally calculate between-group effect sizes at each timepoint. Effect sizes will be expressed as Cohen’s *d* with 95% confidence intervals. In addition, a clinically significant change will be examined using the reliable change index [25].

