**Variable**				
*Primary:*				
Perceived Stress	x	x	x	
*Secondary:*				
Absenteeism	x			x
Mental Health	x	x	x	
Teacher skills	x	x	x	
Pupil-teacher relationship	x	x	x	
*Possible mediators:*				
Self-compassion	x	x	x	
Mindfulness skills	x	x	x	
Emotion regulation skills	x	x	x	

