### Secondary outcome measures

#### Absenteeism

Teachers are asked about their absenteeism of the past year between the first and last day of the schoolyear (how many days they called in ill and with which frequency). In addition, teachers are requested to record their absence and frequency in the current year. To support this data, their records will be verified with the schools’ absence system.

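### Absenteeism is taken from teachers' own reports, with the school absence system used only to verify them, so a teacher who returns no end-of-year record has no stated route to a trial-year value

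*Protocol article*

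**What the plan says.** The Absenteeism section of the protocol article names the teacher as the source for both school years. For the prior year, "Teachers are asked about their absenteeism of the past year between the first and last day of the schoolyear". For the trial year, "teachers are requested to record their absence and frequency in the current year". The school's system comes in afterwards: "their records will be verified with the schools’ absence system".

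Table 1 schedules absenteeism at baseline and at the end of the school year (July), with nothing at post-test or at the 3-month follow-up. The section Procedure and allocation adds: "We will compare data related to teacher absenteeism from the school year prior to that in which they participate in the research".

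For non-response, the Data collection section provides online reminders, then a telephone call, and reasons are noted if participation ends. School records are not mentioned there. The Effectiveness section states: "The primary analyses will be based on the intention-to-treat principle". The Sample size calculation allows for loss: "With an estimated 17.5% drop-out, which is comparable to a similar study".

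**The concern.** Of the listed outcomes, absenteeism is the one that could in principle be obtained without the teacher's continued cooperation. The plan nevertheless ranks the teacher's record first and the school's record second. Verification needs something to verify, and a teacher who returns nothing gives no starting point.

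The loss is unlikely to be random. The Background section links continued stress to absenteeism and to leaving the profession. Teachers on long sick leave may be among those least likely to keep and return a record. Contact with the study also differs by arm before July: the MBSR course ends in November, while wait-list teachers are offered theirs after the March follow-up. Return rates could therefore differ by arm, although the document gives no evidence that they will.

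At stake is whether secondary aim (a) compares all randomised teachers or only those who stayed in contact.

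**Working it through.** **1. The plan's own figure.** Inputs from the Sample size calculation: α 0.05 (taken as two-sided), standardised effect 0.50, power 80%, drop-out 17.5%. The two-sample t-test calculation gives 63.77, so 64 per arm and 128 in total. Inflation: 128 / (1 − 0.175) = 128 / 0.825 = 155.15, against 155 stated. The figure reproduces, and nothing here depends on it being wrong.

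**2. How many values could be lost.** 155 × 0.175 = 27.1, or about 27 teachers, leaving about 128. This is an upper illustration. The 17.5% is a general drop-out allowance taken from a similar study, not a rate of unreturned July absence records.

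**3. What the model can recover.** Absenteeism has a baseline and a July value only. If it is analysed as the Effectiveness section describes for continuous outcomes, the baseline score is a covariate. A teacher without the July value then has no post-baseline observation and adds essentially nothing to the treatment contrast. Baseline adjustment helps only with loss that is predictable from prior-year absence.

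**4. How selective loss acts.** Let an arm have true mean μ, a fraction f lost, and mean d among those lost. The mean among those observed is

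(μ − f·d) / (1 − f) = μ − [f / (1 − f)]·(d − μ).

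If f and d − μ are the same in both arms, the same amount is subtracted from each and the between-arm difference is unbiased. Bias needs f or d − μ to differ by arm.

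**5. Illustration.** All absence figures and arm-specific rates are assumed; the document gives none. No true effect, μ = 10 days in each arm, d = 20 days. Each pair of rates averages 17.5%.

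| Loss MBSR / wait-list | Observed mean MBSR | Observed mean wait-list | Spurious difference (MBSR − wait-list) |
|---|---|---|---|
| 17.5% / 17.5% | (10 − 3.5)/0.825 = 7.88 | 7.88 | 0 |
| 20% / 15% | (10 − 4)/0.80 = 7.50 | (10 − 3)/0.85 = 8.24 | −0.7 days |
| 15% / 20% | 8.24 | 7.50 | +0.7 days |
| 25% / 10% | (10 − 5)/0.75 = 6.67 | (10 − 2)/0.90 = 8.89 | −2.2 days |
| 10% / 25% | 8.89 | 6.67 | +2.2 days |

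The sign follows whichever arm loses more. No standard deviation for absence days is given, so these differences cannot be set against sampling error.

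**6. Precision.** Assuming a standardised effect of 0.50 for absenteeism (the document states none), t-test power is about 80% with 128 teachers and about 87% with 155. The effect detectable at 80% power falls from about 0.50 to about 0.45.

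**The case against.** A reader might infer that every teacher who stops answering loses this outcome while the school still holds it. The document does not support that:

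- It never says that school data will go unused when a teacher gives no record. A fallback may stand in the full protocol, the analysis plan or the data management plan, none of which is shown.
- The prior-year value is collected at baseline, so only the trial-year value is at risk.
- Missing the November or March questionnaire does not by itself remove the July record, and telephone follow-up is provided.
- That the school holds the data is an assumption, weakest for teachers who change school or leave the profession.

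A reader might also infer that self-report by teachers who know their arm leaves the outcome unprotected from reporting bias. It does not, since verification against the school system partly addresses this for those who return a record.

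Finally, verified self-report is a legitimate design, the outcome is secondary, and the trial was under way when the article was written (version dated 23-11-2020). By then cohort 1's July 2020 point and cohort 2's September 2020 baseline had passed.

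These points limit the claim and its size. What remains is that the order of sources is stated, not merely left out: the teacher reports and the school system verifies. That puts the source that depends on response ahead of one the team already means to consult.

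**Conclusion.** The point holds in limited form. As written, a teacher who returns no end-of-year record has no stated route to a trial-year absence value, and neither the non-response procedure nor the mixed model supplies one. The loss is plausibly related to the outcome. It biases the comparison if its amount or selectivity differs by arm, and the bias is nil if both are equal. Neither direction nor size can be derived from the document. The only figure it offers is the ceiling of about 27 of 155 teachers, which rests on applying the general drop-out allowance to this outcome. The primary outcome and the sample size are unaffected. The change is worth making because it concerns a named secondary aim and extends access that is already planned.

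**What to change.** - For the trial year, and for the prior year where available, take days and number of spells from the school absence system as the main source. Do this for every randomised teacher whose consent covers it, including those who stopped the course or the questionnaires.
- Use the teacher's report where no school record exists, for example after a change of school. Report agreement between the two sources among teachers who have both.
- Apply the same source rule to all three cohorts, extracting retrospectively for earlier cohorts within existing consent, so that the source does not change between cohorts.
- At withdrawal, record whether it covers the questionnaires only or access to absence records too.

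The cost should be small. Schools are already to be approached for verification, most belong to one overarching organisation (Procedure and allocation), and a protected key linking pseudocodes to names exists (Data collection). The downside is a somewhat larger extract, and incomplete coverage where earlier consent or the schools' records do not allow it. That shortfall should be reported by arm.

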#### Mental health

Mental Health Continuum-Short Form [32]. Emotional, psychological and social well-being will be assessed using self-report on the 14-item Mental Health Continuum-Short Form (MHC-SF). Each item is scored on a 6-point rating scale ranging from 0 (*never*) to 5 (*every day*) with higher scores indicating more positive mental health. The Dutch version shows high internal consistency for the total MHC-SF score (*α* = .89) and the two subscales Emotional and Psychological Well-Being (both α = .83), and adequate for the third subscale Social Well-Being (α = .74) [32]

#### Teacher skills

Teacher Self Efficacy Scale Short Form (TSES-SF; alpha .76; 10 items [33];). This scale measures four areas directly related to successful teaching, namely job accomplishment; development possibilities within the workplace; social interaction with pupils, parents and colleagues; and coping with work pressure/stress. This questionnaire consists of 10 items on a 3-point Likert scale and has nine subscales from 1 (nothing) to 9 (great deal). Cronbach’s *α* coefficient in previous studies was higher than .75 [34].

#### Classroom climate and pupil-teacher relationship

We will use the teacher questionnaire of the Climate Scale (De Klimaatschaal [35];). This questionnaire consists of 33 items all scored on a 4-point scale ranging from ‘almost never’ till ‘often’. This measures four areas from teachers’ perception of the quality of the classroom climate, the pupil-teacher relationship, the inter-pupil relationship and the experienced order in the classroom. Cronbach’s *α* coefficient >.70 ([36], p.33).

### Potential mediators

#### Self-compassion

Self-Compassion Scale-short Form [37]: The short form of the Self Compassion Scale (SCS-SF) will be used to measure self- compassion. This instrument consists of 12 items based on a 7-point Likert scale and measures six components of self-compassion: Self-kindness, Self-judgement, Common Humanity, Isolation, Mindfulness and Overidentification. The shortened scale shows a near-perfect correlation with the original Self Compassion Scale. In a Dutch population, Cronbach’s *α* coefficient for the full scale is .87 and the coefficients for the subscales of the SCS-SF vary from .55 to .81 [38].

#### Mindfulness skills

The Five Facet Mindfulness Questionnaire Short Form [39]: We will use the short form of the Five Facet Mindfulness Questionnaire (FFMQ-SF) to measure mindfulness skills. This self-report questionnaire consists of 24 items, which are rated on a 5-point Likert scale. Five facets of mindfulness are distinguished: Observing, Describing, Acting with Awareness, Non-judging and Non-reactivity. The Dutch version of the FFMQ-SF has been shown to be a reliable instrument, which is sensitive to change in a population with depressive and anxiety symptoms. Cronbach’s *α* coefficients between .75 and .87 have been found [40].

#### Emotion regulation skills

BRIEF-A [41]: The self-report version for adults of the Behaviour Rating Inventory of Executive Function (BRIEF-A) will be used to measure executive functioning in daily life. This questionnaire consists of 75 items on a 3-point Likert scale and has nine subscales: Inhibit, Shift, Emotional Control, Self-monitor, Initiate, Working Memory, Plan/Organise, Task Monitor and Organization of Materials. Three validity scales are included: Negativity, Infrequency and Inconsistency. The Dutch version shows a good internal consistency for the global executive composite score and both indexes (Cronbach’s *α* coefficient ranging from .92 to .96) and sufficient internal consistency for all subscales [42].

### Qualitative research

To get more in-depth insight into the effects of the MBSR-training, qualitative interviews with teachers will be conducted between 8 and 10 weeks after participating in the MBSR training. Purposive sampling will be used to include a subset of teachers with different backgrounds. The interviews will be semi-structured focusing on the main topic: How did the MBSR programme affect your ability to function as a teacher?

We will process and analyse the qualitative data by using Atlas.Ti. Interviews will be audio-recorded and transcribed verbatim. We will return a summary of the interview to the participants for member-checking. Two independent raters will code the data to minimize subjectivity. We will begin analysis as soon as the first data are collected and will continue with each additional interview. The constant comparison method will be used to analyse the data until saturation has been reached. This procedure is comparable to those used in other qualitative studies (e.g. [43]).

## Discussion

There is a lack of evidence-based effective interventions targeting stress/work-related problems in primary school teachers. At the same time, many school organizations are looking for a way to reduce teachers’ stress perception and to reduce absenteeism without loss of quality with regard to teaching, education quality, or pupils’ achievements. From previous studies, it can be concluded that MBSR is a promising intervention for stress reduction in healthy subjects [7, 15–17]. However, it is unknown whether MBSR is appropriate and effective for stress-reduction in teachers in primary education. The aim of this study is to examine the effectiveness of MBSR on primary school teachers’ perceived stress, absenteeism and mental health, their teaching skills (with an emphasis on emotion regulation), classroom climate and pupil-teacher relationship.

### Strengths and limitations

A strength of the current study design is that it not only assesses immediate effects, but also includes a follow-up after 3 months. This will allow us to test both the short- and mid-term effects of the MBSR programme. We also included a broad set of outcomes.

Second, the implications of this study may be important for both the regular and academic training of primary school teachers. If the present study indicates that the programme is effective in reducing stress, these educational systems may structurally integrate the programme into their curriculum, thereby increasing both the personal resilience and the professional development of teachers nationwide. A third strength of the study is that the trainer in the present study has a longstanding career as a teacher and principal in primary education in addition to being a qualified mindfulness teacher.

The present study also has several limitations. Firstly, although school weight will be used for stratification, the study population based on initial recruitment and the pilot study will be predominantly from urban areas. This might limit generalizability to areas with other demographic characteristics such as rural areas. However, research shows that teachers in rural areas experience less stress compared to those in urban areas [44]. Due to the current growing shortage in teachers in urban areas [45], the discrepancy between teachers’ stress levels in urban versus rural areas may increase further. The fact that only one trainer delivered the programme could be considered another limitation of the study, as this might compromise the generalizability of the results. Should this study demonstrate that the MBSR programme is effective among teachers, further research should be set up with a broader diversity in the setting of schools and mindfulness trainers.

## Trial status

Protocol paper 23-11-2020 version 1

Recruitment started: 19-06-2019

Approximate date recruitment will be completed: August 2021

## Data Availability

The datasets used and/or analysed during the current study are available from the corresponding author on reasonable request. A data management plan has been created under supervision of [name], research Data Officer of the Behavioural Science Institute. This plan can be obtained from the first author. The results of the trial will be published in peer-reviewed international journals and presented at international conferences.

## Abbreviations

RCT: Randomized controlled trial
MBSR: Mindfulness-based stress reduction
TNO: Nederlands organisatie voor Toegepast-Natuurwetenschappelijk Onderzoek (the Netherlands Organization for applied scientific research)
CBS: Centraal Bureau voor Statistiek (Statistics Netherlands)
MBI: Mindfulness-based intervention
PSS: Perceived Stress Scale
MHC-SF: Mental Health Continuum-Short Form
FFMQ-SF: The Five Facet Mindfulness Questionnaire Short Form
SCS-SF: Self-compassion Scale Short Form
IRB: Internal Review Board
ECSW: Ethische Commissie Sociale Wetenschappen (Ethics Committee of Social Sciences)
DUO: Dienst Uitvoering Onderwijs (the implementation organization of the National Government for Education)
ICC: Intraclass correlations
TSES-SF: Teacher Self Efficacy Scale Short Form
AVS: Algemene Vereniging Schoolleiders (Dutch association school leaders)
